## Abstract

**Simple Summary:**

The management of advanced colorectal cancer (CRC) has been greatly improved with integrated strategies including stereotactic radiation therapy (SRT). It is a safe and effective option, particularly in oligo-metastatic (om) CRC patients. Interestingly, it has been demonstrated that SRT can induce regression of tumors in non-irradiated regions (“abscopal effect”) through stimulation of anti-tumor immune effects (“radiation-induced immunity”). We have recently shown that lung-limited omCRC is characterized by regression of tumor clones bearing specific key driver gene mutations. The aim of the PRELUDE-1 study is to assess the genetic and immunologic evolutions on tumor cancer/host cells induced by SRT in lung-limited omCRC through liquid biopsies and Next Generation Sequencing of tumor exome, HLA repertoire assessment, peripheral immune cells, and cytokine dynamics characterizations. An important secondary objective is the first prospective evaluation of the abscopal effect. The PRELUDE-1 results will help to identify subsets of patients more prone to show the abscopal effect. The PRELUDE-1 trial was registered into the clinicaltrials.gov registry on 22 April 2021, with identifier NCT04854213.

**Abstract:**

Background: in recent years, the management of advanced colorectal cancer (CRC) has been greatly improved with integrated strategies including stereotactic radiation therapy (SRT). The administration of SRT has been demonstrated, particularly in oligo-metastatic (om) CRC, to be a safe and effective option. Interestingly, it has been demonstrated that SRT can induce regression of tumors in non-irradiated regions (“abscopal effect”) through stimulation of anti-tumor immune effects (“radiation-induced immunity”). We have recently shown that lung-limited omCRC is characterized by regression of tumor clones bearing specific key driver gene mutations. Aims: to assess the genetic evolution on tumor cancer cells induced by SRT in lung-limited omCRC. Secondary objectives included descriptions of the abscopal effect, responses’ duration, toxicity, and progression-free survival. A translational research will be performed to evaluate tumor genetic evolution (through liquid biopsies and Next Generation Sequencing), HLA class I repertoire, peripheral immune cells, and cytokine dynamics. Methods: PRELUDE-1 is a prospective translational study. SRT will be administered only to the largest nodule (with a maximum diameter ≤ 25 mm) in omCRC with two or three radiologically evident lesions. The sample size is based on the innovative hypothesis that radiation-induced immunity could induce regression of tumor clones bearing KRAS oncogene mutations. According to the binomial test, considering the frequency of KRAS mutations and assuming a probability of mutant KRAS→wild type KRAS of p_0_ = 0.0077, with α = 0.05 and 1-β = 0.60, the final sample size is 25 patients.

## 1. Introduction

Colorectal cancer (CRC) represents the third most frequent cancer in both sexes. Unfortunately, more than 30% of patients are diagnosed with metastatic and unresectable disease mostly involving the liver [1]. Lungs and lymphnodes are also frequently targeted by metastatic CRC (mCRC). Chemotherapy (fluoropyirimidines, oxaliplatin, irinotecan) and biologic drugs (bevacizumab, aflibercept, cetuximab, panitumumab) have improved survival, which in rare cases can surpass 30 months [2]. Furthermore, in recent years, integrated strategies including stereotactic radiation therapy (SRT) have shown to be effective, particularly in oligo-metastatic CRC (omCRC) [3]. The omCRC clinical setting is represented by patients bearing indolent and low-burden mCRC. However, its definition is elusive and difficult. In fact, besides the tumor burden (≤3 lesions per organ with a total tumor size ≤7 cm) [4,5], it should also be considered the “rate of metastases development” [6,7,8]. However, to date, the immunologic and genetic characteristics underlying the oligo-metastatic phenotype are largely unknown and unexplored. We have recently shown that lung-limited omCRC is characterized by regressive mutations in key driver genes, suggesting that the oligo-metastatic status relies on atypical genetic evolution of cancer [9].

In recent years, the following considerations prompted the use of SRT in the treatment of omCRC: (i) the opportunity to delay the start of more toxic therapeutic approaches; (ii) the radio-sensitivity of colorectal cancer; (iii) the amelioration of the technique (sparing of healthy tissue and high and hypo-fractionated irradiation doses); and (iv) the increasing availability of the technique. 

## 2. Trial Rationale

### 2.1. Rationale for Evaluating the “Abscopal Effect” in omCRC

The “abscopal effect” (from Latin abscopus) is the anti-tumor effect elicited away from the target. In fact, high-dose radiotherapy (clinically used in hypo-fractionated regimens of SRT) can stimulate anti-tumor immune effects: “radiation-induced immunity” [10,11,12,13,14,15,16]. SRT is based on a great precision of tumor targeting allowing the use of high-doses in a hypo-fractionated manner. Oligo-metastatic cancers with controlled primary lesions are the ideal setting for SRT. Previous studies demonstrated that SRT is able to improve survival in lung-limited omCRC patients with median survivals approaching to three years. Significant prognostic factors are the number and the volume of lung metastases [17,18,19]. Unfortunately, the presence of occult microscopic tumor cell deposits at other sites is responsible for therecurrence and development of new distant metastases after SRT. Interestingly, hypo-fractionated SRT determines specific changes in the immune contexture of tumors characterized by the increase of human leukocyte antigen (HLA) class I expression, of antigen-presenting cells (APCs), of cytotoxic T lymphocytes (CTLs), of natural killer (NK) cells, and of interferon(IFN)-gamma secretion [20,21,22]. The last cytokine concurs to increase intracellular peptide levels through enhanced tumor antigens degradation. Hypo-fractionated radiation alsoinduces cell death by upregulating Fas and many other cytokines such as interleukin (IL)-2, IL-1α, IL-1β, IL-12, and tumor necrosis factor (TNF)-α involved in the initiation of an adaptive anti-tumor immune response [11,23,24,25,26,27,28]. These immunologic phenomena may be responsible for anti-tumor effects away from the irradiated target. Interestingly, a study by Lee et al. showed that the anti-tumor properties of high-dose radiotherapy associates with recruitment and priming of T cells in immune-competent mice; the same cancer was radio-resistant in immune-deficient or CD+ T-cell depleted animals [10]. 

### 2.2. Rationale for Evaluating Immune Regulatory Cells

Soluble mediators (cytokines, chemokines, etc.) and effector/regulatory lymphocytes participate in the orchestration of anti-tumor immunity through a dynamic balance between activation and inhibition of the immune response. In fact, many innovative drugs act by revitalizing the anti-tumor response [29]. The hypothesis that regulatory effectors can influence the extent of radiation-induced immunity deserves to be verified. The most important actors in the negative regulation of immune responses are: T regulatory cells (Tregs), myeloid-derived suppressor cells (MDSCs), and tumor-associated macrophages (TAMs) [30,31,32,33,34]. Interestingly, both MDSCs and Tregs increase in the peripheral blood (PB) of preclinical tumor models and suppress T-cell functions, which, in turn, favors cancer proliferation and metastases [35]. Tregs characterized as CD4+CD25+ T cells are fundamental in preserving self-tolerance and thus avoiding autoimmune activation [36,37,38,39,40,41,42]. They inhibit T cell activation through the secretion of immune-suppressive cytokines (IL-10, IL-35, TGF-beta, etc.) or surface expression of PD-L1 [41,42]. MDSCs are immature, myeloid cells able to inhibit the anti-tumor responses [43,44]. MDSCs secrete suppressive cytokines (e.g., IL-10, arginase, TGF-beta, etc.) that inhibit T cells and stimulate Tregs and M2 macrophages [33]. It was previously demonstrated that MDSCs and Tregs’ basal values are significantly increased in locally advanced rectal cancer (LARC) patients who received neoadjuvant chemo-radiotherapy before surgery versus healthy donors. Moreover, LARC-poor responder patients had a higher amount of Tregs in peripheral blood [45].

### 2.3. Human Leukocyte Antigens (HLA) and Anti-Cancer Immune Response

T cells’activation is based on sequential phases starting into specialized lymphoid organs. T cell precursors recognize tumor-derived peptide epitopes/HLA complexes on APCs through their T-cell receptors (TCRs) [46,47,48,49]. The binding between specific peptides processed by the proteasome system and specific HLA molecules occurs in the cytoplasm of APCs. Several algorithms have been developed to predict the binding affinity between epitopic sequences and HLA molecules [50,51,52,53,54]. In fact, polymorphisms of HLA-I alleles account for a different probability of tumor peptide recognition and subsequent activation by tumor-infiltrating T cells. Thus, patients with different class I and II HLA haplotypes have differential immune reactivity to the same tumor epitopes (CTL priming, expansion, and activation). For this reason, in the PRELUDE-1 study HLA haplotypes will be evaluated to adequately interpret eventual abscopal effects in lung-limited omCRC and to generate hypotheses on tumor-derived peptides’ repertoire.

### 2.4. Rationale for Evaluating Genetic Evolution of Cancer through Liquid Biopsies

The cancer genome is highly heterogeneous and dynamic. Mutation gains in some genes prompt cancer progression and resistance to therapy. Study of these changes is crucial to understand cancer biology and to propose innovative treatments. The most direct method to assess cancer genetics relies on the sampling of tumor tissues and its molecular characterization through whole genome sequencing techniques [55,56]. However, some issues can limit these evaluations since (i) biopsies are invasive and cannot be easily repeated during the treatments, (ii) tumor tissue is not always available, (iii) the genetic fingerprint of the neoplasia can change during the time due to the clonal selection of the host environment and to the different treatments. Alternatively, liquid biopsy is a non-invasive method to characterize cancer DNA, which can be repeated over time and which can collect circulating cancer material coming from all the clones of the neoplasia [57]. The technique is based on assessing tumor DNA released into the blood of cancer patients. In fact, it is well known that at least three cancer-associated phenomena concur to enrich the blood flow of tumor DNA: apoptosis, cell necrosis, and active secretion. Therefore, circulating tumor DNA (ctDNA) represents the tumor fingerprint in the blood. Next-generation sequencing (NGS), whose complete dissertation is beyond the scope of this study, is a suitable and reliable tool for genetic characterization through liquid biopsy in CRC [58,59]. 

Identifying the genetic and immunologic evolutions of cancer, in time and space, is a new and challenging issue. The introduction of high-throughput genetic assessments including NGS has enormously prompted this aspect of cancer research. Such an approach is providing novel and unexpected insights in cancer biology and suggesting new therapeutic strategies. Many studies in pmCRC have revealed heterogeneous results in the genetics of primary tumors (PT) and “matched” metastatic lesions (as evidenced by the occurrence of *de novo* mutations) with concordance rates (shared point mutations/total number of point mutations) ranging from 0 to 100% [60,61,62,63,64]. 

### 2.5. Definition of “Genetic Regression”

In a previous study in lung-limited omCRC, we documented changes of KRAS status in metastatic formalin-fixed and paraffin-embedded (FFPE) tumor tissues compared to the primary ones (KRAS was mutated in primary tumor but not in subsequent metastases) [9]. These genetic trajectories were associated with a good prognosis as observed also in omCRC with liver-limited disease [65] and poly-metastatic CRC [66]. Therefore, we defined “genetic regression” as the loss of the genetic alterations in a specific key-driver gene from the primary tumor to the metastatic one (i.e., mutant KRAS (mutKRAS) in primary tumor→wild-type KRAS (wtKRAS) in metastases). This issue was opposed to “progressive” genetic trajectory (i.e., wtKRAS in primary tumor→mutKRAS in metastases) where the metastatic lesions gain genetic alterations advantageous for the tumor development [67]. RAS proteins (specifically, KRAS and NRAS) are small GTPases along the epidermal growth factor receptor (EGFR) pathway [68,69]. When activated by ligand/receptor binding, RAS protein releases GTP, binds to GTP, and, in turn, activates crucial kinases(i.e., RAF proteins, phosphoinositide 3-kinase (PI3K)-AKT, etc.) involved in several cancer-related phenomena (migration, survival, adhesion, growth, and differentiation) [70]. These data indicate that omCRC tumor clones may follow regressive genetic trajectories differing from those of cancer cells with poly-metastatic behavior.

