## 3. Trial Design

### 3.1. Objectives

#### 3.1.1. Primary Objective

The primary objective is to verify that SRT can induce regression of KRAS mutant clones into the entire metastatic mass in a clean model of oligo-metastatic CRC. 

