### 3.2. Design and Sample Size Calculation

PRELUDE-1 is a prospective, translational, and proof-of-principle study to detect regression of KRAS mutations in CRC induced by SRT. It will be conducted at the academic hospital Istituto Nazionale Tumori di Napoli, IRCCS “G. Pascale” in Naples (Italy). The sample size of the PRELUDE-1 study is based on the innovative hypothesis that radiation-induced immunity could induce regressive trajectories in metastases bearing KRAS oncogene mutations (i.e., mutKRAS→wtKRAS). 

According to the binomial test, considering a frequency of KRAS mutations of 50.0% (the study is not restricted to KRAS mutated patients) and assuming a probability of mutKRAS→wtKRAS of p_0_ = 0.0077 [9], with α = 0.05, 1-β = 0.60, p = the *a priori* success rate, and X = the number of patients with mutKRAS→wtKRAS, the final sample size is 25 patients. With the algorithm $P\left(X,N,p\right)=\left(\begin{array}{c} N\\ x \end{array}\right)p^{x}{\left(1-p\right)}^{n-x}$, the regressive trajectory is statistically relevant if mutations occurs in >2 out of the planned 25 patients.

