### 3.11. Timing of Exams and Procedures

Timings and types of procedures are synthesized in Figure 1 and Table 1.

Screening phase. Inclusion and exclusion criteria will be evaluated during the screening phase.

Baseline phase. Thereafter, after signing the informed consent, a venous blood sample (10 mL) for the liquid biopsy (LB) will be collected coinciding with the routine assessment before the SRT start. Baseline visit (clinical history, clinical examination, PS ECOG, vital signs) and exams (including basal LB (LB-T1)) will also be carried out within 14 days before the SRT start. Blood count and clinical biochemistry will be performed at our local laboratories. The following parameters will be assessed: blood count with leukocyte formula, hemoglobin, platelets, total bilirurbin, AST, ALT, alkaline phosphatase, serum creatinine, total proteins, sodium, potassium, calcium, urea, lactic dehydrogenase, creatinine clearance, CEA, and CA19.9. Patient’s heart rhythm and conduction will be evaluated with ECG. The ventricular ejection fraction will be assessed with cardiac ultrasonography.All potentially childbearing women musthave a negative pregnancy test during the screening phase. If requested by the local ethics committee, the test can also be repeated during treatment. Barrier methods for anti-conception must be used by all patients throughout the duration of the study. FDG-PET and total-body computed tomography with iv contrast or, if contraindicated, magnetic resonance (MRI) abdomen and high-definition chest-computed tomography without iv contrast will be performed. 

Treatment phase. Clinical examination and evaluation of vital signs will be performed at each radiotherapy visit. Cardiological evaluation, CEA, CA19.9, and assessment of response to treatment will be performed after 40 days and 2 months from the radiotherapy start and, thereafter, every 3 months until progression. 

“Interval” phase. LB-T2 will be performed 40 days after major nodule irradiation coinciding with post-RT cell blood count and biochemical assessment along with CT total-body-scan and FDG-PET. Thereafter, the disease will be monitored every three months, and non-irradiated nodules will be treated in case of volumetric progression according to clinical practice in oligo-metastatic disease.

End-of-study phase. The study ends after LB-T2 assessment. 

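### The primary event is not tied to the samples before and after SRT, so KRAS loss that predates SRT could be counted as a success

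*Protocol article*

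**What the plan says.** - **Definition (Protocol article, 2.5).** Genetic regression is "the loss of the genetic alterations in a specific key-driver gene from the primary tumor to the metastatic one", exemplified as "mutant KRAS (mutKRAS) in primary tumor→wild-type KRAS (wtKRAS) in metastases". It arose from the sponsor's earlier study of tissue in lung-limited oligometastatic CRC (reference 9).
- **Objective (3.1.1).** "The primary objective is to verify that SRT can induce regression of KRAS mutant clones into the entire metastatic mass". Section 3.2 likewise calls the trial a study "to detect regression of KRAS mutations in CRC induced by SRT".
- **Sample size (3.2).** The hypothesis is that "radiation-induced immunity could induce regressive trajectories in metastases bearing KRAS oncogene mutations (i.e., mutKRAS→wtKRAS"). The counted event is given as "X = the number of patients with mutKRAS→wtKRAS, the final sample size is 25 patients". The null rate p0 = 0.0077 is cited to reference 9. The KRAS mutation frequency is 50%, enrolment is not restricted to mutated patients, and the result is positive if more than 2 of 25 patients show the event.
- **Samples (3.4, 3.9, 3.11, Table 1).** Resected primary tissue is required and sequenced. On LB-T1, the text says "exams (including basal LB (LB-T1)) will also be carried out within 14 days before the SRT start". LB-T2 follows 40 days after irradiation. No sampling of metastatic tissue is described.
- **Comparison of samples (3.8).** Concordance percentages and Venn diagrams compare samples in general; no pair is named as primary.

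**The concern.** The objective needs a contrast across SRT. The stated definition spans a longer interval, from the resected primary to the metastasis, and so includes whatever happened before irradiation. Section 3.2 uses the definition's notation and its source study without naming the start and end samples.

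With a threshold of three patients, one or two whose KRAS mutation was already gone at LB-T1 could decide the result. Such loss would then be read as an effect of SRT, although the sample that could show otherwise is already planned. If those patients are excluded because the event is meant as LB-T1 to LB-T2, the null rate no longer matches the event tested.

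**Working it through.** **The two readings**

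| | Event is primary → metastasis (2.5) | Event is LB-T1 → LB-T2 (implied by 3.1.1 and 3.11) |
|---|---|---|
| Matches the only definition | Yes | No |
| Matches the source of p0 | Yes, apart from plasma in place of metastatic tissue | No: p0 is a tissue rate from primary to metastasis |
| Isolates change after SRT | No | Yes |
| Wild-type at LB-T1 with a mutated primary | Can count | Cannot count |

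Neither column satisfies the definition, the null rate and the objective together.

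**The plan's own figure**

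Inputs from 3.2: N = 25, p0 = 0.0077, α = 0.05, power 0.60, positive if X > 2, that is X ≥ 3. The alternative rate is not stated, so N = 25 cannot be uniquely reproduced. Solving back for 60% power at N = 25 gives an alternative of 0.121 with the written rule, or 0.079 if the rule were at least 2. Under p0 the expected count is 25 × 0.0077 = 0.19 and P(X ≥ 3) = 0.0009.

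**Sizing the first reading**

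Let q be the share of KRAS-mutated primaries already wild-type at LB-T1. The documents do not give q, so it is an assumption. Further assumptions: 50% of primaries mutated (from 3.2), no SRT effect, and patients wild-type at LB-T1 stay so at LB-T2 and are counted. Then

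p = 0.50 × q

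P(X ≥ 3) = 1 − (1−p)^25 − 25p(1−p)^24 − 300p²(1−p)^23

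For q = 10%, p = 0.05, and 1 − 0.277 − 0.365 − 0.231 = 0.127.

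| q | p | Expected count, 25p | P(X ≥ 3) |
|---|---|---|---|
| 1.54% | 0.0077 | 0.19 | 0.0009 |
| 5% | 0.025 | 0.63 | 0.024 |
| 10% | 0.05 | 1.25 | 0.127 |
| 20% | 0.10 | 2.5 | 0.463 |

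The probability passes 0.05 at about q = 6.7%. The first row is the q that p0 implies if p0 is a rate over all 25 patients: 0.0077/0.50 = 1.54%. If p0 is a rate among mutated patients only, the overall rate is 0.00385 and P(X ≥ 3) = 0.00012.

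**The case against.** The strongest reply is that a before/after comparison was plainly intended. The definition sits in the rationale and reports an earlier study. Section 3.2 starts from metastases that carry the mutation, and a patient wild-type at LB-T1 does not fit that wording. LB-T1 and LB-T2 bracket the irradiation, and without metastatic tissue the definition cannot be applied word for word. All of this stands. A reader might infer that such patients certainly would be counted; the text supports only that they could be. But intent is not a counting rule, and the only definition given says something else.

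A second reply is that, on the primary-to-metastasis reading, p0 is the matched natural-history rate, so the test already allows for earlier loss. This is right as far as p0 is right for these patients: at q of about 1.5% the error is negligible, and even at 5% it is below α. A reader might infer that p0 is refuted by the Introduction, which says "We have recently shown that lung-limited omCRC is characterized by regressive mutations in key driver genes" and cites the same study. The documents do not support that. The sentence concerns several genes and gives no rate, whereas p0 is for KRAS alone. There is tension, not contradiction.

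Nor does p0 come from a different disease setting, as a reader might infer. Section 2.5 places the earlier study in lung-limited oligometastatic CRC. What differs is the sample type and the absence of a contrast across SRT.

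**Conclusion.** The point holds as a conflict between the definition, the null rate and the objective, not as proof that patients will be miscounted. Either KRAS loss before SRT can count toward a threshold of three patients, or p0 belongs to a different contrast from the one tested. This is more than detail left to a fuller document, because the article states a definition that does not fit its own primary objective.

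On the first reading, the chance of a positive result without any SRT effect runs from 0.0009 (q = 1.5%) to 0.463 (q = 20%) and exceeds 0.05 above about q = 6.7%. These figures rest on an assumed q, 50% mutated primaries and the written rule of at least 3 of 25. The documents do not show that q is large. They also give no safeguard if it is, since no section requires a KRAS mutation at LB-T1.

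**What to change.** 1. Define the primary event as KRAS mutation detected at LB-T1 and not detected at LB-T2, with ctDNA shown to be present at LB-T2, so that an absence of tumor DNA is not read as loss of the mutation.
2. Report change from primary tumor to LB-T1 separately, as pre-SRT change that does not count toward the test.
3. State that p0 = 0.0077 is a tissue-based rate from primary to metastasis, and show the result over a range of p0.
4. Mark the definition in 2.5 as that of the earlier study, and name the sample pair for X in 3.2.

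**Cost.** No new samples are needed. Patients with a mutated primary but a KRAS-negative LB-T1 cannot be successes. If the denominator is limited to patients mutated at LB-T1, at most about 25 × 0.50 = 12.5, so 12 to 13, are expected. The null rate, the rule of more than 2 of 25 and the stated power must then be restated.

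Removing patients who were never mutated costs little power in itself. With a rule of at least 3, 60% power needs a rate of 0.121 over all 25, or 0.121/0.50 = 0.243 among mutated patients. With 13 or 12 patients it needs 0.229 or 0.247. The real loss comes from mutated patients who are KRAS-negative at LB-T1. A range of p0 displays the sensitivity but does not supply a null rate for a change over the interval from LB-T1 to LB-T2, so the sponsor would still have to justify one.
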